#### N-back

During the fifth day of each study arm, participants are asked to undertake a cognitive test measuring aspects of working memory. In this task, a series of letters will appear on the screen one at a time. The participant needs to make a response as to whether the letter that he sees each time on the screen matches a letter presented previously (= reference letter). This continuously changing reference letter depends on instructions that appear at the beginning of each of the many letter sequences. If the appearing letter matches the reference letter, he should press a button labelled as “same”, and in all other cases a button labelled as “different”. In the one-back task, the reference letter is every previous letter, in the two-back test the reference letter is every second previous letter and in the three-back test every third previous letter. All data are anonymously stored in the University of Bristol computers.

The n-back task captures the active part of working memory. When n equals 2 or more, it is not enough to simply keep a representation of recently presented items in mind; the working memory buffer needs also to be updated continuously to keep track of what the current stimulus must be compared to. To accomplish this task, the subject needs to both maintain and manipulate information in working memory. This task has been shown to activate frontal and parietal cortical regions, among them the dorsolateral prefrontal cortex [38]. Moreover, the n-back has a good test-retest reliability in terms of the neural processing recruited for this cognitive task [39], while behaviourally, daily practice for a duration of weeks is required to gain any significant benefits in performance [40] independent of any experimental conditions.

#### Functional and perfusion imaging

During the fifth day of each study arm, participants undergo a specific brain MR scanning protocol. The protocol consists of two block-designed task-based fMRI paradigms (see Fig. 3), a resting state fMRI, a pseudo-continuous arterial spin labelling-based perfusion imaging scan (using six post-labelling delays; 0.25 s, 0.50 s, 0.75 s, 1.00 s, 1.25 s, 1.5 s), as well as a number of supportive MRI sequences. The temporal design of the MR scanning protocol is based on the results of study stage 1 (see below and Table 4). Table 5 presents some technical details about the MRI experiment, following the guidelines for reporting an fMRI study, as presented in Poldrack et al. [41]. To confront with the low test-retest reliability of the facial expression processing task [39], as with FERT, we are introducing different facial stimuli per testing session. Note that the mean test-retest period is anticipated to be larger than 14.6 days, which is the one tested in Plichta et al. [39].

**Fig. 3 Fig3:**

Tasks of controlled block design used during the functional neuroimaging protocol. **a** During the implicit facial expression processing task, individuals are exposed to alternating visual stimuli (pictures) consisting of 30-second blocks of human faces with a particular facial expression (fear -F- or happiness -H- or sadness -S). Each block corresponds to one kind of facial expression, where 10 different human faces, male or female, with the same facial expression are presented for 0.1 second with a 2.9-second inter-stimulus interval. Blocks are divided from each other by resting state periods (lasting 30 seconds). Each kind of block (F, H, S) is repeated four times. The paradigm starts and finishes with a resting state period. Participants are given a button box and explicitly instructed to press a corresponding button depending on whether the face they see each time is male or female (gender discrimination). Both accuracy and response time are recorded. **b** During the flashing checkerboard task, individuals are visually exposed to a flashing checkerboard (a checkerboard whose cells alternate between white and black colours with a frequency of 7.5 Hz) for 16 seconds followed by a resting period of 15 seconds before the next flashing checkerboard visual stimulation initiates. The resting period-flashing checkerboard alternation is repeated 10 times. Subjects are instructed to have their eyes open and look at the screen all the time

**Table 4 Tab4:** Temporal design of study stage 2 and the concurrent relative glucocorticoid dynamics per study group

		Cortisol dynamics		
		Ultr.	Circ.	PO
MRI scanning protocol	08:45–10:00 am			
• Localizer	08:45–09:05 am	*D*	*S*	*D*
• TOF_3D_Neck	08:45–09:05 am	*D*	*S*	*D*
• EPI_2D_Resting State	08:50–09:10 am	*S*	*S*	*D*
• EPI_2D_Zshim_calibration	09:00–09:15 am	*A*	*S*	*D*
• EPI_2D_Zshim_IFEPT	09:05–09:30 am	*A*	*S*	*D-S*
• EPI_2D_pCASL	09:20–09:45 am	*A*	*S*	*D-S*
• GRE_field mapping	09:35–09:50 am	*A*	*S*	*D-S*
• EPI_2D_Zshim_FCT	09:40–09:55 am	*S*	*S*	*D-S*
LSEQ	10:00–10:20 am	*D*	*S*	*S*
Oxford P1vital ETB	10:15–10:50 am	*D*	*S*	*S*
N-back	11:10–11:40 am	*D-S*	*S*	*S*
Oxford P1vital EPST	12:05–12:50 pm	*A*	*S-D*	*S-D*

Non-task scans will include perfusion imaging (pCASL), supportive imaging to reduce geometric distortions (Z-shimming calibration and field mapping) to allow for increased accuracy of analysis, and resting state imaging to assess functional connectivity. The EPI_2D_Zshim_calibration sequence is specifically designed to reduced signal dropout from the orbitofrontal cortices. 2/3D: two-/three-dimensional, *A* ascending cortisol levels, *pCASL* pseudo-continuous arterial spin labelling, *Circ.* circadian (without the ultradian component), *D* descending cortisol levels, *EPI* echo planar imaging, *ETB* emotional test battery, *EPST* emotion potentiated startle task, *FCT* flashing checkerboard task, *GRE* gradient recalled echo, *IFEPT* implicit face expression processing task, *LSEQ* Leeds Sleep Evaluation Questionnaire, *PO* per os, *S* steady (no significant changes in) cortisol levels, *TOF* time-of-flight, *Ultr.* ultradian and circadian rhythm, *Zshim* shimming along the Z axis

**Table 5 Tab5:** Technical image properties of the three functional MR sequences used for data acquisition

	MRI system		
	Siemens Magnetom Skyra syngo MR D13C (3 tesla)		
	MRI acquisition details		
	IFEPT	FCT	RS
Volumes	250	105	180
Pulse sequence type	EPI	EPI	EPI
FOV	192 mm	192 mm	192 mm
Matrix size	64x64 mm	64x64 mm	64x64 mm
Slice thickness	3 mm	3 mm	3.5 mm
Acquisition orientation	T > C-30.0 > S2.3	T > C-30.0 > S2.3	T > C-30.0 > S2.3
Whole brain?	Yes	Yes	Yes
Bandwidth	2298 Hz/Px	2298 Hz/Px	2170 Hz/Px
Order of acquisition	Interleaved	Interleaved	Interleaved
TE	30 ms	30 ms	28 ms
TR	3,000 ms	3,000 ms	2,040 ms
Flip angle	87°	87°	89°

*C* coronal, *EPI* echo planar imaging, *IFEPT* implicit face expression processing task, *FCT* flashing checkerboard task, *FOV* field of view, *RS* resting state imaging, *S* sagittal, *T* transverse (axial), *TE* echo time, *TR* repetition time

The determination of the brain regions of interest (ROIs) in our study is based on the following criteria: (1) areas which are glucocorticoid-sensitive (that is, express glucocorticoid and mineralocorticoid receptors) according to the most up-to-date knowledge [42–46], while at the same time (2) are implicated in (face) emotional processing and mood regulation [47–51]. Based on the above criteria, eight ROIs have been pre-selected: amygdala, prefrontal cortex (with particular focus on orbitofrontal cortex), insular cortex, dorsal striatum (part of basal ganglia), nucleus accumbens (part of ventral striatum), hippocampal formation, and anterior and posterior cingulate cortex.

### Power analysis: how many subjects in study stage 2?

With a sample size of 15 participants on whom complete data are available, we will have 80 % power at an alpha level of 5 % to detect an effect size equivalent to f = 0.35. This is our current best estimate of the likely effect size across the three conditions of our study, based on work in other settings using pharmacological challenge (for example, antidepressants) to probe these psychological mechanisms.

### Data analysis for study stage 2

For the EMA data, the area under the curve will be calculated for measures of tiredness and mood. These will be used as the primary outcome variable. Secondary analyses will be conducted on other derived variables, such as the degree of variability in tiredness and mood over time (that is, amplitude). In ETB and n-back tasks, interpretation of the neurobehavioural phenotypes will result from co-evaluating the percentage of correct and false responses, the mean latency of correct responses (in milliseconds) and percentage of non-responses among the different study groups [35, 52]. The recorded task measures of accuracy, reaction times, and — where relevant — signal magnitude will be grouped according to relevant stimulus properties such as valence (positive/neutral/negative) and analysed for effects of pharmacological treatment using analyses of variance (ANOVA). In EPST, the presence and magnitude of eye blinking in response to white noise will also be grouped according to relevant stimulus valence (positive/neutral/negative) and compared across the three different groups using ANOVA. This will also be done in LSEQ.

At the individual level, functional imaging data will be pre-processed to remove the influence of external factors like magnetic field inhomogeneities and motion artefacts, extract the brain from the skull and other soft tissues, co-register different imaging modalities (low-resolution functional images with the corresponding high-resolution anatomical image) with a standard reference template (MNI152). Prior to model estimation, the time series blood oxygen level-dependent (BOLD) data will be temporally filtered (high pass) and spatially smoothed in an effort to improve the signal-to-noise ratio. A general linear model will be applied to the task-based fMRI data to estimate BOLD signal change associated with each paradigm. Subsequent group effects will be assessed via mixed effects inference with a Bayesian two-level model with fast approximation to posterior probability of activation using Functional Magnetic Resonance Imaging of the Brain (FMRIB) Software Library (FSL) software [53] in combination with statistical parametric mapping (SPM) software [54]. Other techniques will be recruited to explore functional connectivity of the brain.

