### Study stage 2: randomisation and blinding

The second stage of the study is the randomised, double-blinded, placebo-controlled, three-way crossover investigation, where participants undergo all three optimised five-day treatment schemes as finalised in the previous stage. Randomisation schedules were generated using IBM SPSS® v19 software by staff members not directly involved in data collection for this study. Dispensing and processing of all medication/placebo is managed by Bristol Royal Infirmary University Hospital Pharmacy, ensuring that study researchers remain blinded to the conditions. To ensure that the study remains double-blind, all participants are required to take the same daily regime of tablets and remain connected to a subcutaneous pump (continuous or pulsatile). Each week one of these treatments will be placebo (either placebo tablets or 0.9 % saline infusion via the pump). In addition, the study investigators responsible for care of the pumps have no input into the psychological testing. There is a minimum of two weeks between each of the three study arms. Participants and study researchers are therefore unaware of the order of the arms of their hydrocortisone replacement.

On day 1 of each arm, participants are connected to the pump via a line that is inserted into the subcutaneous tissue of the abdomen and are trained to handle the pump by themselves (detach-reattach). Participants are given metyrapone and identically encapsulated tablets containing either hydrocortisone or placebo and the investigator explains to them the five-day treatment plan they will follow. The participants receive instructions in cases of an emergency (hypoadrenal symptoms). Finally, they also receive their study android phone that monitors their everyday state of mood and reactivity at random points within each day (see below). Participants also give a urine sample to be tested for the presence of drugs of abuse.

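### Two AUCs, tiredness and mood, are jointly called the primary outcome with no rule for which decides, so depending on the rule either the 5% alpha or the 80% power can fail

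*Protocol article*

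**What the plan says.** The section on power for stage 2 gives one calculation. "With a sample size of 15 participants on whom complete data are available", it says, "we will have 80 % power at an alpha level of 5" per cent "to detect an effect size equivalent to f = 0.35". The effect size is described as "our current best estimate of the likely effect size across the three conditions of our study". No outcome is attached to the figure.

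The next section, on data analysis for stage 2, names the primary outcome for the phone-based momentary assessments: the "area under the curve will be calculated for measures of tiredness and mood. These will be used as the primary outcome variable". The subject of that second sentence is plural and the outcome it names is singular.

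Stage 2 is a "three-way crossover investigation, where participants undergo all three optimised five-day treatment schemes", so the natural test of the stated effect size is an omnibus comparison of three conditions within each participant.

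**The concern.** One alpha and one power figure describe one test. Here at least two variables carry the primary label, and the article does not say how they combine into a conclusion. Four rules are compatible with the text: either AUC suffices, both are needed, the two are merged into one score, or one is ranked ahead of the other. They differ in error rate and in power, and only some of them agree with the figures printed beside them. If the rule is still open when results are seen, the AUC that supports a claim can be chosen afterwards, and the 5% no longer describes the risk of a false primary finding.

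**Working it through.** **Inputs from the article.** n = 15 completers; m = 3 conditions, all within person; f = 0.35; alpha = 0.05; two AUCs.

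**Inputs assumed, because the article gives none.** Within-person correlation rho between conditions (0.5 as base, varied below); sphericity; correlation r between the two outcomes' within-person errors (0 to 0.9); for the power results, the same f for both AUCs.

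**1. Reproducing the stated power.** For a repeated-measures omnibus F test, the noncentrality is lambda = f² × n × m / (1 − rho), with (m − 1) = 2 and (n − 1)(m − 1) = 28 degrees of freedom.

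- lambda = 0.35² × 15 × 3 / 0.5 = 0.1225 × 45 / 0.5 = 11.03.
- The critical value of F(2, 28) at 5% is 3.34, and power is 81.1%.
- With n = 14 power is 77.8%, so 15 is the smallest sample reaching 80%.

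The printed figure is therefore right for one test at rho = 0.5. It moves with rho: 73.1% at 0.4 and 89.3% at 0.6.

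**2. Either AUC suffices, each tested at 5%.** With independent outcomes the family-wise error is 1 − 0.95² = 9.75%. Simulating pairs of these F tests under the null (1,000,000 pairs per setting) gives:

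| r | Family-wise error |
|---|---|
| 0 | 9.8% |
| 0.5 | 9.2% |
| 0.7 | 8.5% |
| 0.9 | 7.2% |

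Power per outcome stays at 81%. The chance of at least one success, when both effects are f = 0.35, is 96% at r = 0 and 86% at r = 0.9. Only the 5% fails.

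**3. Alpha split, 2.5% each.** The critical value rises to 4.22. Power per outcome at n = 15:

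| rho | lambda | Power at 2.5% |
|---|---|---|
| 0.4 | 9.19 | 61.9% |
| 0.5 | 11.03 | 71.4% |
| 0.6 | 13.78 | 82.1% |

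At rho = 0.5 the detectable f at 80% power rises from 0.346 to 0.382, and 80% power per outcome at f = 0.35 would take 18 completers (81.4%). The 5% holds; the 80% fails at rho = 0.5 or below, but not at 0.6.

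**4. Both AUCs required, each at 5%.** The error rate cannot exceed 5%. Joint power at rho = 0.5 is 66% at r = 0 and 76% at r = 0.9. The 5% holds and the 80% fails.

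**5. One AUC ranked first, the other tested only if the first succeeds.** Both tests run at 5% and the family-wise error is held at 5%. Power for the first-ranked AUC is 81.1%, as printed. Power to claim the second as well equals the joint power in step 4, 66% to 76%.

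**The case against.** The strongest reply is that this is a condensed article, and that the order, split or joint rule for several outcomes is commonly left to an analysis plan, which is not shown. That stands for the adjustment method, and silence on it is not the point. Which variable is primary and what the power figure covers are different: the article states both, and states them in a way that does not fit together. The singular noun might point to a composite score, but no combination is described.

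Three stronger readings are tempting and are not supported.

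- A reader might infer that the 5% and the 80% both fail. No single rule examined above does that. Unadjusted either-wins testing breaks the error rate and leaves power intact; a split, or requiring both, protects the error rate and can cost power.
- A reader might infer that the tests will be uncorrected and that either AUC will count as success. The article says neither, so the 7% to 10% is conditional on that rule.
- A reader might doubt f = 0.35 because of where it came from. The article says openly that it is "based on work in other settings using pharmacological challenge (for example, antidepressants) to probe these psychological mechanisms"; antidepressants are an example, and the sources cannot be examined here. This is a separate question and adds nothing to the present one.

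The study is also introduced as a physiological pilot in healthy volunteers. That lowers the stakes. It does not remove the mismatch, because the article itself claims 80% power at 5%.

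**Conclusion.** The point holds as an ambiguity in the primary decision rule. The power calculation is correct for one omnibus within-subject test, given rho of about 0.5 and sphericity. It cannot be read as covering two co-equal primaries without a rule.

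The size depends on the rule: a family-wise error of about 7% to 10% instead of 5%, or about 71% power per outcome at rho = 0.5, or 66% to 76% joint power. The power losses rest on an assumed rho; at 0.6 a split alpha would still give 82%. The error range rests on an assumed correlation between the two AUCs, for which the article offers no value. Of the rules compatible with the text, a ranked order (for its first AUC) or a pre-stated composite keeps both printed figures. Severity is moderate.

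**What to change.** Before unblinding, name one AUC as primary. Mood is a natural candidate, since the section on research questions and hypothesis names mood and does not mention tiredness. Test the other AUC only if the first is significant, each at 5%. Restate the power line so that the 80% refers to the first-ranked AUC, in one omnibus within-subject test with 15 completers and f = 0.35, under an assumed within-person correlation of about 0.5 and sphericity.

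If both AUCs are to stay co-equal, use Holm's procedure and state power of about 71% per outcome at its first step, under the same assumptions.

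The cost is wording only, and the article reports the trial as still recruiting at submission. No more participants are needed. The price is that the second AUC becomes conditional on the first or, under Holm, that the stated power is less favourable.

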## Discussion

This project aims to investigate the impact of dynamic changes in glucocorticoid rhythmicity on neural processing of emotional perception as well as cognitive and behavioural phenotypes in healthy male individuals, utilising functional imaging of the brain and a series of cognitive and psychological tests. To test this we are using a double-blind, three-way crossover randomised design. This will allow us to perform within-subject analysis, comparing three methods of hydrocortisone delivery: oral, (subcutaneous) continuous and (subcutaneous) pulsatile.

Determination of the inclusion and exclusion criteria was based on a number of known neuroendocrinological and neurophysiological factors that could alter HPA axis function and bias results. Nicotine, alcohol and caffeine [55–57] are known to elevate cortisol and are carefully controlled for at screening and then during the study. Concurrent use of other prescribed drugs (especially steroid-based) or recreational substances may also influence HPA axis function [58], and may confound functional neuroimaging data [59].

Only male individuals were recruited for this study, as there is a sexually dimorphic difference in the behaviour in response to cortisol [60, 61] and functional variations in the neuroanatomical distribution of glucocorticoid-mediated cognitive and emotional processing [62, 63]. In relation to our study, a recent meta-analysis [64] has indicated a sex-dependent difference in the effect size of the BOLD signal response of amygdala after exposure to emotional faces, which is one of the main fMRI paradigms we use. In addition, response of female individuals to hydrocortisone is modulated by oral contraceptive use and varies over the menstrual cycle [65], with the latter being difficult to control for, given the crossover nature of the study.

In this study the control of handedness is also important, as there is evidence for a positive relationship between degree of handedness and degree of cerebral lateralisation for processing emotional faces in men [66]. Dyslexia has been related to impaired processing of rapid stimulus sequences [67] similar to the ones used in our study, and was therefore controlled for.

The issue of cultural differences and the extent of universality in emotional perception is very complex. In general, happiness, anger and (dynamic) non-verbal channels of communication are parameters that show less cross-cultural variability (that is, are characterised by a lesser within-cultural-group advantage) [68]. During the design of study stage 2, we avoided setting cultural/racial criteria in our recruitment strategy for ethical reasons; rather we chose to primarily rely on investigational tools of emotional perception that show the least possible cross-cultural variability.

General intelligence was not controlled for in this study, as there is no convincing evidence suggesting that the degree of general intelligence is linked to particular patterns of brain morphology [69] or frontal and corticolimbic activation patterns under emotional stimulation [70], which are our regions of interest. Other individual differences (intrinsic environmental and genetic factors) could not be assessed and consequently could not be controlled.

All three methods for creating different daily patterns of circulating glucocorticoids are based on the combined treatment of metyrapone and hydrocortisone. This offers a direct relevance for the treatment of actual patients with hypoadrenalism. Thus, this study could potentially also provide pilot data on whether replication of the ultradian pattern in glucocorticoid-based therapeutics could improve treatment efficiency and attenuate side effects. Even in the case of adrenal insufficiency, replacement therapy under the established therapeutic protocols is accompanied by a higher mortality rate, increased morbidity from poor quality of life (mental and physical fatigue, cardiovascular, malignant and infectious diseases), increased psychosocial needs and morning fatigue compared to normal individuals [71]. The presence of neuropsychiatric symptomatology, and all other iatrogenic problems, in these patients suggests that temporal aspects of glucocorticoid therapy may be helpful in achieving their homeostatic effects rather than their deleterious side effects.

The optimisation process for our metyrapone blockage and hydrocortisone replacement therapy is based on two criteria: (1) the preservation of systemic cortisol levels within a physiological range during hydrocortisone replacement, and (2) the suppression of the endogenous adrenal activity during the 24-hour studies. Endogenous adrenal activity can be biochemically discriminated from exogenous hydrocortisone administration in these participants due to the prolonged interval (10–12 hours) between the last per os hydrocortisone dose of day 4 (around 07:00 pm) and the first hydrocortisone dose of day 5 (around 07:00 am). Based on the above criteria, we have derived the ideal metyrapone treatment dose for study days 4 and 5 as: 0.75 g during breakfast (day 4), 0.75 g during lunch (day 4) and 1 g before going to sleep at night (day 4) and 0.75 g during breakfast (day 5). This treatment strategy effectively suppresses endogenous adrenal activity in a reversible manner and results in plasma cortisol profiles that reliably reflect the pattern of exogenous hydrocortisone administration. This is also confirmed with the subcutaneous hydrocortisone replacement [19, 22] strategies (see Figs. 5 and 6) in two other healthy male volunteers. None of these five participants reported any side effects (expected or unexpected).

During the neurobehavioural investigation, 15 participants will undergo all three methods of hydrocortisone delivery for five days as optimised during the previous study stage. EMA via the android phone will gather daily data about self-perceived mood and emotional reactivity of each subject, during these five-day periods. On the final day of each study arm (day 5), participants will undergo a number of neurobehavioural tests (see Table 4). Based on the biochemical results of the preliminary stage of the study (Figs. 4, 5 and 6), the MR scanning will take place between 8:45–10:00 am. During this period of time glucocorticoid dynamics among the three study groups show distinctly different motifs (see Table 4). The EPST will take place after 12:00 pm to capture the effect of the pulsatile mode of replacement which results in a rising phase in the subjects’ plasma cortisol levels in contrast to the other two study groups. Overall, as seen in Table 4, the exact time periods during which participants are scanned and tested during arm day 5 of study stage 2 correspond to specific phases of circulating cortisol dynamics per treatment strategy.

